#### Control condition

The control condition consists of the delivery of four non-monetary retention items totaling <$20/dyad to the participant’s home. Retention items were selected by the community and provided as a way to continue to stay in contact with families for follow-up data collection.

#### Discontinuing or modifying intervention

Participants will not be allowed to change groups. They will be able to stop participating at the study at any point. Study staff are trained to identify and report adverse events. In the event of an adverse event, the study staff member will call the PI and follow-up with an email detailing the event. All adverse events will be sent to the IRB according to their required schedule. The study will be reviewed by approving IRBs annually. There is no post-trial care or compensation for those who suffer harm from trial participation.

### Recruitment and consent

Participants will be recruited through a combination of non-probability and snowball sampling. First, recruitment fliers will be posted in community gathering spots (i.e., supermarket, community centers, health and human services offices, fitness centers, etc.), on social media (e.g. Facebook) and disseminated during public gatherings through informational booths. Second, caregivers enrolled in the project will be asked to refer other caregivers who may be eligible and interested in the program. Third, IEs will provide information about the study to local agencies that provide services to eligible participants (e.g. Office of Self Reliance, local schools, counseling services etc.) and provide them with referral forms. Independent Evaluators will collect referral forms from these agencies on a regular basis (e.g. weekly). All recruitment materials have contact information for the local project coordinator. To learn about the project and enroll, interested individuals can call the local project coordinator. A study staff member will also reach out to referred caregivers or parents of a referred child. When contact is made with a potential participant, the IE will review a brief script describing the study and assess for eligibility. For those individuals meeting eligibility criteria who express interest in study participation, the study staff member will work with them to set up a time to complete informed consent/parental permission/assent and work with the participant to contact the caregiver who will enroll with them (adolescent and adolescent’s female caregiver). The informed consent process will include a review of how personal information will be collected, shared and maintained to protect confidentiality of the participant’s study data. After both the caregiver and adolescent participants have completed informed consent and adolescent assent respectively, they will complete the baseline assessment and schedule their first lesson.

### Retention

Participants will receive gift cards for participation in assessments ($20 per assessment time point per participant). Additionally, FHCs and IEs will do all they can to keep participants enrolled and engaged including providing transportation to study visits and snacks or meals at these visits. Participants will only be dropped from the program if they request. Outcome data will be collected from all participants regardless of their intervention completion status.

### Outcomes

Assessments will be administered at baseline, immediately following program completion and 6- and 12-months following program completion (see Table 2). Data will be collected in participants’ homes or another private location via a tablet using Research Electronic Data Capture (REDCap). Caregivers will complete all assessments via self-report. Adolescents will complete portions of the outcome assessment asking about sexual and substance use behaviors via self-report. All other portions will be be completed via interview. Participants will be given $20 after completion of the baseline, immediate, six and twelve month post intervention assessments. All measure items were previously piloted with adolescent and caregivers from the community to assess comprehension, language, and cultural relevance. Edits were made accordingly and pilot participants were not eligible for the RCT.

**Table 2 Tab2:** Study Evaluation: constructs measured, method of administration and timepoint administered

Construct Measured	Completed by	Method ofadministration	Timepoint Administered			
			Baseline	Immediate Post	6 month post	12 month post
**DEMOGRAPHICS**						
Age, gender, language spoken in home, housingsituation and education	Caregiver	Self-Report	X	X	X	X
Age, gender, language spoken in home, housingsituation and education	Adolescent	Interview	X	X	X	X
**PRIM****ARY AIMS**						
**Caregiver-Adolescent**	Adolescent	Interview	X	X	X	X
**Relationship** [45, 46]						
Quality time together				X		
Communication^a^				X		
Warmth				X		
Monitoring				X		
**Reproductive Health and intentions about****sexual activity**	Adolescent	Self-Report	X	X	X	X
**SECONDARY AIMS**						
***Adolescent Measures***						
**Individual Level Protective and Risk Factors**						
Self-Regulation [47]	Adolescent	Interview	X	X	X	X
Self-Esteem [47]	Adolescent	Interview	X	X	X	X
Future Aspirations [48]	Adolescent	Interview	X	X	X	X
Perseverance/Resilience [47]	Adolescent	Interview	X	X	X	X
Optimism [47]	Adolescent	Interview	X	X	X	X
Self-Efficacy [47]	Adolescent	Interview	X	X	X	X
Interpersonal Competence [47]	Adolescent	Interview	X	X	X	X
Internalizing and Externalizing behaviors	Adolescent	Interview	X	X	X	X
Reproductive Health Knowledge	Adolescent	Self-Report	X	X	X	X
Self-Regulation [49]	Adolescent	Self-Report	X	X	X	X
Healthy Relationship Knowledge [49]	Adolescent	Self-Report	X	X	X	X
**Cultural Knowledge and Connection**						
Navajo Cultural Knowledge	Adolescent	Interview	X	X	X	X
Participation in Traditional and Religious Activities [50]	Adolescent	Interview	X	X	X	X
Family Engagement in Navajo Culture	Adolescent	Interview	X	X	X	X
**Family**						
Family Conflict, Expressiveness and Cohesion [51]	Adolescent	Interview	X	X	X	X
Parent Expectations and Attitudes [52, 53]	Adolescent	Self-Report	X	X	X	X
**Peer and Trusted Adults**						
Peer Role Models: Youth Asset Survey [48]	Adolescent	Self-Report	X	X	X	X
Peer and Partner Negotiation Skills [49]	Adolescent	Self-Report	X	X	X	X
Communication with Peers [49]	Adolescent	Self-Report	X	X	X	X
Communication with Trusted Adults [49]	Adolescent	Self-Report	X	X	X	X
**Behavioral Intention and Outcomes**						
Substance Use [54]	Adolescent	Self-Report	X	X	X	X
***Caregiver Measures***						
**Mother Daughter Relationship** [45, 46]						
Communication	Caregiver	Self-Report	X	X	X	X
Warmth	Caregiver	Self-Report	X	X	X	X
Monitoring	Caregiver	Self-Report	X	X	X	X
**Individual Level Protective and Risk Factors**						
Parenting Self- Efficacy [55]	Caregiver	Self-Report	X	X	X	X
Parenting Self-Agency [56]	Caregiver	Self-Report	X	X	X	X
Reproductive Health Knowledge	Caregiver	Self-Report	X	X	X	X
Communal Mastery [57]	Caregiver	Self-Report	X	X	X	X
Parent Expectations and Attitudes [52, 53]	Caregiver	Self-Report	X	X	X	X
**Cultural Knowledge and Connection**						
Cultural Connectedness [50]	Caregiver	Self-Report	X	X	X	X
Participation in Navajo practices	Caregiver	Self-Report	X	X	X	X
Experience with Native Language	Caregiver	Self-Report	X	X	X	X
Cultural Knowledge	Caregiver	Self-Report	X	X	X	X
Family engagement with culture	Caregiver	Self-Report	X	X	X	X
**Family**						
Family Conflict, Expressiveness and Cohesion [51]	Caregiver	Self-Report	X	X	X	X
**Behavioral Intention and Outcomes**						
Substance Use [54]	Caregiver	Self-Report	X	X	X	X
**Parent Report on Youth**						
Internalizing and Externalizing behaviors	Caregiver	Self-Report	X	X	X	X
Youth Experience with Substances	Caregiver	Self-Report	X	X	X	X
**OTHER MEASURES REQUIRED BY FUNDER**						
Exit Survey: includes questions about program satisfactionand sexual health behaviors/attitudes [58]	Adolescent	Self-Report		X		

^a^Primary Aim in which sample size was determined

Please see Table 2 for a description of the outcome measures, including method and frequency of administration.

### Data management

All data will be directly entered into REDCap by an intervieweer (IE) or the participant. If assessments are completed via paper, they will be entered by the IE. A data manager will review all data entered into REDCap to ensure completeness and conduct data quality assurance (including checking ranges for variables as applicable). All data will be stored via REDCap, a secure, HIPPA compliant, data collection and storage database. Data will be analyzed part way through the trial by the evaluator. The study management team (including the evaluator, the PI and the program manager) will review data and assess the need to continue the trial.

### Randomization and sample size

This study will use a 1:1 randomized controlled trial design; the unit of randomization will be the individual dyad. Unique participant identification numbers will be used to randomize individual dyads to one of two study groups: intervention or control. Stratified block randomization, using random block size will be used to ensure a 1:1 allocation of study conditions across the two study sites. The sequence will be generated by the program evaluation via STATA and will not be shared with study staff who enroll participants.. Independent Evaluators will enroll participants and reveal study group after the participants complete the baseline assessment. The study assignments are sequentially numbers in sealed envelopes that are only opened at the time of randomization. No blinding will occur.

Sample size and statistical power estimates are predicated on 2 primary hypotheses: 1) that those randomized to the AB intervention will have improved parent-adolescent communication compared to the control group, and 2), that those randomized to the AB intervention group will have a higher proportion of participants who report they intend to abstain from sex.

The sample size of 410 dyads (*n* = 205 per study arm) will be sufficient to detect a 0.3 difference between study groups, with 90% power and 0.05 significance level, on the communication scale at 12 months post-intervention (estimating a mean score (SD) of 2.81(0.85) in the control group). This same sample size will be sufficient to detect an 18% between-group difference, with 80% power and 0.05 significance level, in the proportion of participants who report intention to abstain from sex at 12 months post-intervention (estimating 50% of the control group to report intention to abstain from sex at 12 months post-intervention). This sample size will also be able to detect meaningful differences in other key confirmatory research question outcomes at 12 months post-intervention. The following presents minimum detectable differences between the intervention and control groups with at least 80% power, given the assumptions listed above: 0.39 between-group difference in internalizing behaviors (estimating a mean score (SD) of 5.23 (0.99) in the control group), and 0.25 between-group difference in externalizing behaviors (estimating a mean score (SD) of 2.04 (0.63) in the control group). All estimates assume 10% attrition between enrollment and program completion and a 25% attrition rate between program completion and the 12 month follow-up time point.

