#### Study staffing

This study is being conducted at two study sites on the Navajo Nation. The Center has had a physical office and has conducted projects in partnership with the Navajo Nation for over 30 years. Each site has two family health coaches (FHCs), one independent evaluator (IE) and one site coordinator. Other members of the study team, including the principal investigator, program manager, program coordinator and evaluator, are located at the Center’s administrative office in Baltimore, Maryland. The field manager is located in Arizona near the Navajo Nation. All members of the study team are full-time Johns Hopkins employees and are thoroughly trained in human subjects research prior to working with participants. Members of the Baltimore team and the field manager make frequent trips (at least bi-annual) trips to the study sites to conduct training and quality assurance.

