#### Independent evaluators

Independent Evaluators are Navajo women living in one of the two study communities. All speak some Navajo. All IEs will complete extensive training (> 40 h) in the study protocol including recruitment, consenting and data collection. IEs will recruit participants, administer informed consent, receive parental permission and adolescent assent. IEs will also administer all assessments and provide gift cards for assessment completion.

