#### Site coordinators

Site Coordinators are Navajo women living in one of the two study communities. They will provide on-site support to all local study staff.

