This study also has limitations. First, all outcomes are measured via self-report and/or via interview. While self-report is the most widely used methodology to assess behavior change, it is not without biases. There are also potential biases in interview administration, such as… [70]. However, steps have been taken to reduce potential biases. The IEs are highly trained in evaluation administration and human subjects research and will not deliver any part of either AB program or condition non-monetary gifts, limiting potential evaluator bias. Other methods to reduce bias include: 1) all IEs will be Native women from the local community, 2) the same IE will conduct the baseline and all follow-up assessments for each dyad, 3) all interviews will be conducted in person (vs. some in person and some via telephone/video call), and 4) the most sensitive questions focused on actual behavior and behavioral intention are conducted via self-report (not interview).

Another limitation is that the follow-up time period is only 1 year. Since adolescents are 10–14 years of age when enrolling in this program, we do not expect a large proportion of adolescents to initiate substances or have sex by the 12 month follow-up timepoint. Thus, we do not expect to have adequate power to assess impact of AB on actual behaviors. However, we will have power to assess the impact of AB on behavioral intention. Studies indicate there is a strong, positive association between intention to abstain from sex and delayed sexual initiation [71]. Further, we will assess key protective factors that are associated with delayed sexual initiation and substance use among Native and non-Native adolescents [19, 23, 71].

Third, there is potential for some contamination between control and intervention groups, as this study will be conducted in a small communities where many families know each other. To limit contamination, we will individually randomize dyads and assign siblings to the same randomization group.

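### The evaluator who reveals the study group then interviews the same girl at every follow-up, so the interviewer for the Communication endpoint knows the arm by design; the article's safeguards do not address this.

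*Protocol article*

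**What the plan says.** Randomization and sample size: "Independent Evaluators will enroll participants and reveal study group after the participants complete the baseline assessment", followed by "No blinding will occur".

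Independent evaluators: "IEs will also administer all assessments and provide gift cards for assessment completion".

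Study staffing: "Each site has two family health coaches (FHCs), one independent evaluator (IE) and one site coordinator". With the Discussion's statement that "the same IE will conduct the baseline and all follow-up assessments for each dyad", one person at each site follows every dyad from baseline to 12 months.

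Outcomes: the girls self-complete the sexual and substance use items, and then "All other portions will be be completed via interview". Table 2 agrees. It lists the girls' Caregiver-Adolescent Relationship scales (quality time, communication, warmth, monitoring) as Interview, and reproductive health and sexual intentions as Self-Report. The Communication row carries the footnote marking it as the aim that set the sample size. Caregivers self-complete all their own measures, which include communication, warmth and monitoring.

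On bias, the Discussion says that the evaluators "will not deliver any part of either AB program or condition non-monetary gifts, limiting potential evaluator bias". It also relies on training, local Native evaluators, the same evaluator throughout, in-person interviews, and self-report for the most sensitive questions.

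**The concern.** Communication is one of the two outcomes on which power is based, and a girl gives her answers to it aloud to someone who told her family which arm they were in. Knowledge of the arm can affect such an interview in two ways. The interviewer may probe or record differently, and the girl may give the answer she thinks a person who knows she had the program would like to hear. Both would tend to favour the program.

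The stated safeguards deal with a different problem. Keeping evaluators out of delivery stops them from rating their own work, but it does not stop them from knowing the assignment. Using the same evaluator throughout helps consistency, yet it carries that knowledge to every follow-up. A larger sample does not cure a differential bias, and no later analysis can reliably remove it.

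**Working it through.** **1. Does the interviewer know the arm?** Four statements, read together, settle it:
- The evaluator reveals the group (Randomization and sample size).
- Evaluators administer all assessments (Independent evaluators).
- The same evaluator returns for every follow-up of a dyad (Discussion).
- The relationship scales are by interview (Outcomes; Table 2).

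So the interviewer knows the arm at all three follow-ups. None of the Discussion's safeguards conceals it.

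**2. Does the evaluator's listed work need that knowledge?** The listed tasks are recruitment, consent, assessment and gift cards. Family health coaches deliver both the program and the control gifts, so they must know the arm. The site coordinator's role is general: "They will provide on-site support to all local study staff". Two loose ends remain. Recruitment and consent has the dyad schedule its first lesson right after baseline. Retention has coaches and evaluators both helping with transport and refreshments at study visits.

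**3. The plan's own sample size.** Inputs from Randomization and sample size: difference 0.3, SD 0.85, 90% power, significance level 0.05, attrition 10% then 25%.
- Retention = 0.90 × 0.75 = 0.675, and 205 × 0.675 = 138.4 evaluable per arm.
- A one-sided 0.05 test at 90% power needs 138 per arm; 138 / 0.675 = 204.4, rounded up to 205, or 410 in all. The figure reproduces.
- With a two-sided test, power at 138.4 per arm is 83.5%. The article does not state sidedness. That is a separate matter, but it confirms 138 per arm as the basis for step 4.

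**4. What a differential reporting bias would do.** The article gives no bias size, so b is assumed. Take no true effect and a two-sided 0.05 test.
- SE = 0.85 × √(2/138) = 0.102.
- Rejection rate = 1 − Φ(1.96 − b/SE) + Φ(−1.96 − b/SE).

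| Assumed b (points) | b / SD | b / 0.3 target | Rejection rate |
|---|---|---|---|
| 0 | 0 | 0% | 5.0% |
| 0.05 | 0.06 | 17% | 7.8% |
| 0.10 | 0.12 | 33% | 16.5% |
| 0.15 | 0.18 | 50% | 31.1% |

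With all 205 per arm retained, b = 0.10 gives 22.2%: more data makes the bias more likely to be declared an effect.

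**5. How much of this masking could remove.** Here b is the whole differential bias, including what comes from girls knowing their own arm. The interviewer's share is unknown. If b = 0.10, perfect masking would leave 16.5% if the interviewer's share is nil, 7.8% if it is half (residual 0.05), and 5% if it is all of b.

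**The case against.** The strongest reply is that this is a declared choice rather than a slip. The article says openly that nobody is blinded, lists interview bias as a limitation, claims only to limit it, and appears to mean by independent that evaluators deliver neither condition. All of that stands, so the article does not contradict itself here. The point is a design improvement.

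A second reply is that masking would be fragile. There is one evaluator per site, the communities are small, visits may be in the home, families know their arm, and a single slip unmasks every later interview of that dyad. This also stands. A reader might infer that the interviewer could readily be blinded and the bias avoided; the article does not support that. Imperfect masking would, however, leave the trial no worse off than the stated plan.

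Third, the outcome is the girl's own report, and she is unblinded whoever interviews her. A reader might take the 8%, 16% and 31% as the error caused by the evaluator knowing the arm. They are not: the biases are assumed, they represent total reporting bias, and a fully self-completed scale with the same bias would give the same rates.

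Fourth, nothing shows that site coordinators attend baseline visits, which may be in homes up to 50 miles away. This stands as a practical cost.

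Two further inferences should be resisted. Concealment before enrollment is not in question: assignments are in sealed envelopes and revealed after baseline. And the article says that the evaluator reveals the group, not who physically opens the envelope; the exposure is the same either way.

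**Conclusion.** The point holds as a worthwhile, low-cost improvement. The interviewer for the girls' relationship scales, including the Communication endpoint, knows the arm by design, and the listed safeguards do not touch that. The exposure covers one of the two powered primary outcomes. Intention to abstain is self-completed and less exposed, so the concern does not extend to the trial's primary evidence as a whole.

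Trial design also names adolescent functioning as primary, and the girls' internalizing and externalizing measure is by interview. Table 2 files that measure under secondary aims, so the conclusion does not rest on it.

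The size cannot be derived from the article. The illustration (about 8%, 16% and 31% for total biases of 0.05, 0.10 and 0.15 points) rests on SD 0.85, 138 per arm, no true effect and a two-sided 0.05 test. Masking would remove an unknown part of it.

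**What to change.** - Once the evaluator confirms that baseline is complete, have the site coordinator or a family health coach, not the evaluator, reveal the assignment and schedule lessons. Keep the envelopes sealed until then.
- Hide allocation from the evaluator in REDCap.
- Give the program-satisfaction exit survey after the interview, self-completed out of the evaluator's view, since the same evaluator returns at 6 and 12 months.
- Have the evaluator record any unmasking: when, and how.
- Replace the statement that there is no blinding with one that evaluators are masked where possible, while families and coaches are not.
- Pre-specify the caregiver self-report communication, warmth and monitoring scales, already collected at every timepoint, as a cross-check on the girls' interview results. Table 2 lists no caregiver version of quality time.

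Self-completion of the relationship scales by the girls is optional. It would reduce the interviewer's influence even where masking fails, but it changes the mode of administration for ages 10–14. If adopted after enrollment has started, it should apply from baseline for new dyads in both arms.

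Cost: an extra contact step at randomization, which existing staff could take on if the coordinator or coach can be reached at that moment. Masking will sometimes fail, and reporting bias from unblinded girls will remain. The sample size does not change.

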### Statistical analysis

The between study group equivalence of participant characteristics and outcome measures at baseline will be compared using Chi-squared tests (dichotomous/categorical data) and t-tests (continuous data). Study hypotheses related to the confirmatory questions will be initially tested under an “intent-to-treat” model in which data are analyzed according to treatment assignment at randomization. We will then conduct “completer analyses” on those subjects completing at least two-thirds of intervention sessions. Intervention impact will be evaluated by comparing primary study outcomes between intervention and control groups across the three time points: baseline, 6 months and 12 months post-intervention. Initially, summary scores of outcomes will be stratified by participation in the intervention versus control groups and by time point, and will be compared using chi-square tests (binary or categorical outcomes), t-tests and analysis of variance (continuous outcomes). Generalized linear mixed effects models (GLMM) accounting for within-group correlation across longitudinal data will then be applied. Outcomes will be modeled as a function of group assignment and time since intervention. The association between outcomes and time will be explored visually using scatterplots and lowess smoothers. Restricted cubic splines will be added to reflect deviations from linearity.

If siblings enter the study, they will be randomized to the same intervention group to limit contamination. In this case, analyses will be adjusted to take into account intra-sibling correlation as well. Additionally, sensitivity analyses will be conducted including and excluding siblings to examine the impact on study results. Missing data will be handled as follows: 1) identify erroneous data, 2) document reason(s) for missing and erroneous data to inform model development; 3) compare demographic characteristics of those who dropped out and those who did not to compare if data is missing at random; and 3) conduct sensitivity analysis to compare inferences that are based on different plausible reasons for missingness. Navajo and Hopkins investigators will collaborate with community partners in data interpretation to assure accuracy, cultural acceptance and relevance.

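### The 90% power for the communication scale holds only for a one-sided 0.05 test that the protocol does not state; a two-sided test gives about 83%, and the companion figures rest on another basis.

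*Protocol article*

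**What the plan says.** The section on randomization and sample size gives the design as "The sample size of 410 dyads (*n* = 205 per study arm"), allocated 1:1 by dyad. It says this number "will be sufficient to detect a 0.3 difference between study groups, with 90% power and 0.05 significance level, on the communication scale" at 12 months, "estimating a mean score (SD) of 2.81(0.85) in the control group". The footnote to Table 2 marks communication as the primary aim from which the sample size was determined.

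The same paragraph makes three further statements:

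- 80% power at the 0.05 level for an 18-point difference in intention to abstain, from 50% in the control group.
- A minimum detectable "0.39 between-group difference in internalizing behaviors" (SD 0.99), with at least 80% power under the assumptions already listed.
- A minimum detectable difference of 0.25 in externalizing behaviors (SD 0.63), on the same terms.

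It closes with "All estimates assume 10% attrition between enrollment and program completion and a 25% attrition rate between program completion" and the 12-month follow-up.

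The article does not say whether 0.05 is one-sided or two-sided. The sizing hypothesis is directional: "that those randomized to the AB intervention will have improved parent-adolescent communication compared to the control group". The statistical analysis section says that outcomes "will be compared using chi-square tests (binary or categorical outcomes), t-tests and analysis of variance (continuous outcomes"), followed by mixed models, and does not mention a one-sided alternative.

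**The concern.** A reader who meets a 0.05 significance level beside t-tests, analysis of variance and chi-square tests will normally take it as two-sided. On that reading, 90% power for communication does not follow from the stated difference, SD, sample size and attrition. A null result on the outcome that sized the trial would then be read against a 10% false-negative risk at the target effect. For a two-sided unadjusted comparison that risk is about 17%.

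The companion figures add to the doubt. They are said to share the same assumptions, but no single choice of sidedness and power reproduces them together with the communication figure. The reader therefore cannot recover the intended test from the paragraph.

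**Working it through.** **Inputs**, all from the section on randomization and sample size: 205 per arm; retention 0.90 and then 0.75; communication difference 0.30, SD 0.85; intention 50% against 68%; internalizing 0.39, SD 0.99; externalizing 0.25, SD 0.63; level 0.05.

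**1. Evaluable dyads.** 205 × 0.90 × 0.75 = 138.4, so 138 per arm at 12 months.

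**2. Reproducing the plan's figure.** The standardized difference is 0.30 / 0.85 = 0.353. The normal formula is n per arm = 2 × (SD/difference)² × (z for level + z for power)².

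- One-sided 0.05, 90% power: 2 × (0.85/0.30)² × (1.645 + 1.282)² = 137.5, so 138. Then 138 / 0.675 = 204.4, so 205 per arm and 410 dyads. This is exactly the stated size. The noncentral t gives 90.0% power at 138 per arm.
- Two-sided 0.05, 90% power: 2 × (0.85/0.30)² × (1.960 + 1.282)² = 168.7, so 169 (170 by noncentral t). This does not match 138.

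**3. Two-sided power at 138 per arm.** The standard error is 0.85 × √(2/138) = 0.1023, and 0.30 / 0.1023 = 2.93. Power ≈ Φ(2.93 − 1.96) = 83.4%; the noncentral t gives 83.2%. The difference detectable with 90% power is 0.333.

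**4. Other two-sided readings of the attrition** (noncentral t): 94.6% with none, 92.2% with the 10% only, 87.0% with the 25% only. None gives 90%.

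**5. Companion figures at 138 per arm.** Means by noncentral t, proportions by the normal formula.

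| Outcome | Printed | Two-sided power at printed value | Detectable, two-sided 80% | Detectable, two-sided 90% | Detectable, one-sided 80% |
|---|---|---|---|---|---|
| Internalizing | 0.39 | 90.3% | 0.335 | 0.388 | 0.297 |
| Externalizing | 0.25 | 90.7% | 0.213 | 0.247 | 0.189 |

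The printed 0.39 and 0.25 equal the two-sided 90% values after rounding. For 50% against 68%, two-sided power is 86.4% (83.5% with continuity correction).

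**6. Is there one basis?** If every test is two-sided, communication has 83% power and not 90%. If every test is one-sided, communication is right, but the minimum detectable differences at 80% are about 0.30 and 0.19, further from the printed 0.39 and 0.25 than the two-sided values are.

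**The case against.** The strongest reply is that the design agrees with itself. The sizing hypotheses are directional, and a one-sided 0.05 test returns 410 dyads and 90% power exactly. This stands. It means that a reader who concludes that the 90% is simply a miscalculation, or that enrolment has to rise, goes further than the document allows. It does not settle the matter, because directional hypotheses are common in trials tested two-sided, the article never declares a one-sided test, and the tests it names do not suggest one.

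Second, a reader might infer that the four power statements imply four conflicting sample sizes. They do not. Two-sided, the internalizing and externalizing figures need 103 and 101 evaluable per arm at 80% power, which agree within the rounding of the printed differences. The intention claim says only that 410 dyads are sufficient, and the other two claim at least 80% power; all three are met. What remains is that 0.39 and 0.25 are mislabelled as minimum detectable differences, on the conservative side.

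Third, 83% is the power of an unadjusted comparison, whereas the plan goes on to a longitudinal mixed model that includes baseline. If baseline were used for adjustment, two-sided power at 138.4 per arm would be about 87%, 89% and 92% at assumed baseline correlations of 0.3, 0.4 and 0.5, with 90% reached at about 0.42. This is fair, and it is why the 17% false-negative risk must be stated conditionally. It cannot support the printed 90%, because the article gives no correlation and does not present its power figure as baseline-adjusted.

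**Conclusion.** The point holds as a conditional one. With the plan's own attrition, 90% power for a 0.30 difference on the communication scale requires a one-sided 0.05 test that the document does not state. Under a two-sided, unadjusted t-test on 138 per arm, power is about 83%, and 90% is reached only for a difference of about 0.33. The internalizing and externalizing figures are conservative but follow a different basis (two-sided 90%) from the one that reproduces the communication figure (one-sided 90%).

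The consequences are limited. Even on the less favourable reading the sizing outcome keeps more than 80% power, and every other stated power claim is met. These figures assume equal SDs in the two arms, attrition applied in sequence, and no allowance for sibling correlation, for which the article gives no value.

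**What to change.** State in both the sample size and the statistical analysis sections whether 0.05 is one-sided or two-sided, and recompute all four statements on that basis at 138 evaluable dyads per arm.

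- **If two-sided:** about 83% power for 0.30 on communication (or 90% for 0.33); about 86% for the 18-point difference in intention to abstain (about 84% with continuity correction); minimum detectable differences at 80% power of about 0.34 for internalizing and 0.21 for externalizing.
- **If one-sided 0.05 was intended:** say so explicitly, keep 90% for 0.30 on communication, and correct the minimum detectable differences at 80% power to about 0.30 (internalizing) and 0.19 (externalizing). Power for the 18-point difference is then about 92% without continuity correction.

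The cost is wording only. On the two-sided basis one stated figure becomes less favourable. Enrolment does not change.
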